#### **6.3.2.2.4. Assessment of accumulation**

$R_o$  (the observed accumulation ratio calculated as  $AUC_{0-\tau}$  on day 10 divided by  $AUC_{0-\tau}$  on day 1) and  $RC_{\max}$  (the accumulation ratio calculated as  $C_{\max}$  on day 10 divided by  $C_{\max}$  on day 1) will be derived for each subject.

Scatter plots of  $AUC_{0-\tau}$  and  $C_{\max}$  against day (Day 1 and 10) will be produced. The data points for each subject will be joined with straight lines. Each analyte will be put on one page so as to allow visual comparison of monotherapy with combination.

If  $AUC_{0-\tau}$  is not calculable due to NQ data in terminal phase,  $AUC_{0-t'}$  will be used with  $t'$  being the latest time at which concentration is >NQ for all subjects and days (Day 1 and Day 10) for a given treatment groups within analyte (for example  $AUC_{0-4}$  or  $AUC_{0-6}$  etc).

A formal assessment of accumulation may be performed for UMEC and VI separately through the statistical analysis of individual  $AUC_{0-\tau}$  and  $C_{\max}$  after log-transformation of the data on Day 1 and Day 10. A mixed effect model in line with GSK SOP-CPK-0007 will be fitted to estimate treatment effect. More details will be provided in the RAP.

**6.3.2.2.5. Time-Invariance**

$R_s$  (steady state ratio calculated as  $AUC_{0-\tau}$  on Day 10 divided by  $AUC_{0-\infty}$  on Day1) will be derived for each subject and will be evaluated in a similar manner as assessment of accumulation if data permits.

**6.3.2.2.6. Treatment Comparison of Systemic Exposure**

Systemic exposure of VI and UMEC will be evaluated when administered in combination compared to administration alone using loge- transformed  $AUC_{0-\infty}$  and  $C_{max}$  in a mixed effects model in line with SOP-BMD-4002 by analyte and by parameter. If  $AUC_{0-\infty}$  is noncalculable,  $AUC_{0-t}$  as defined in Section 6.3.2.2.2 may be used instead. More details will be provided in the RAP.

**6.3.2.3. Pharmacokinetic/Pharmacodynamic Analyses**

The relationship between individual maximum and weighted mean heart rate and QTcF, and VI and UMEC systemic exposure ( $C_{max}$ ), will be explored graphically separately by single dose and repeated dose. If a relationship is observed this will be evaluated further with PK/PD model.

**6.3.2.4. Safety Analyses**

Full details of data analyses of safety in the safety population will be presented in Reporting and Analysis Plan (RAP).

The safety data of the safety population will be summarised descriptively and no formal statistical tests will be performed. Summaries of safety data will include adverse events, serious adverse events, vital signs, ECG (weighted mean (0-4h), Maximum value (0-4 hour) and any laboratory data. All safety data will be reported according to the specific treatment the subject received.

**7. STUDY ASSESSMENTS AND PROCEDURES**

This section lists the parameters of each planned study assessment. The exact timing of each assessment is listed in the Time and Events Tables (Section 4.6). Detailed procedures for obtaining each assessment are provided in the Study Procedures Manual (SPM).

Whenever vital signs, 12-lead ECGs and blood draws are scheduled for the same nominal time, the assessments should occur in the following order: 12-lead ECG, vital signs, blood draws.

Prior to being enrolled in the study and any study procedures being performed, subjects must sign the informed consent.

Each subject will undergo screening procedures within 21 days of the administration of their first dose of study medication and will have a follow up visit between 7 to 10 days inclusive post their last dose. See Section 4.6. for assessments performed at the screening and follow-up visits.

The timing and number of planned study assessments including safety or pharmacokinetic assessments may be altered during the course of the study based on newly available data (e.g. to obtain data closer to the time of peak plasma concentrations) to ensure appropriate monitoring. The change in timing or addition of time points for any planned study assessments must be approved and documented by GSK, but this will not constitute a protocol amendment. The IRB/IEC will be informed of any safety issues that require alteration of the safety monitoring scheme.

No more than 350 mL of blood will be collected over the duration of the study, including any extra assessments that may be required.

## **7.1. Demographic/Medical History Assessments**

The following demographic parameters will be captured: date of birth, gender, race and ethnicity.

Medical/medication/alcohol history will be assessed as related to the eligibility criteria listed in Section 5.2.

## **7.2. Safety**

Planned time points for all safety assessments are listed in the Time and Events Table (Section 4.6). Additional time points for safety tests (such as vital signs, physical exams and laboratory safety tests) may be added during the course of the study based on newly available data to ensure appropriate safety monitoring.

### **Physical Exams**

- A complete physical examination will include assessments of the head, eyes, ears, nose, throat, skin, thyroid, neurological, lungs, cardiovascular, abdomen (liver and spleen), lymph nodes and extremities. Height and weight will also be measured and recorded.
- A brief physical examination will include assessments of the skin, lungs, cardiovascular system, and abdomen (liver and spleen).

### **Vital Signs**

- Vital sign measurements will include systolic and diastolic blood pressure and pulse rate.
- Resting heart rate and blood pressure measurements will be made at screening, at various occasions throughout the treatment periods, and, at the follow-up visit as outlined in Section 4.6 Time and Events Table.
- Three measurements will be taken at screening, 1 – 5mins apart. The mean value recorded will be classed as baseline.
- Subject will be required to rest in the sit position for at least 5mins before each reading.

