### 4. INVESTIGATIONAL PLAN

#### 4.1. Study Design/Schematic

This is a single centre, randomized, open label, 3-period crossover, balanced incomplete block study in healthy Chinese subjects.

All subjects will attend the unit for screening within 21 days of their first of three dosing periods. Each subject will receive three of the five treatment regimens described in [Table 1](#) below.

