**Table 1 Regimens of the study**

| Regimens | Treatments (inhaled once daily for 10 days) |              |
|----------|---------------------------------------------|--------------|
|          | NDPI Strip 1                                | NDPI Strip 2 |
| A        | UMEC 62.5µg                                 | VI 25µg      |
| B        | UMEC 125µg                                  | VI 25µg      |
| C        | UMEC 62.5µg                                 | N/A          |
| D        | UMEC 125µg                                  | N/A          |
| E        | VI 25µg                                     | N/A          |

N/A=Not Applicable

The order in which these treatments are administered will be in accordance with the randomisation schedule, and there will be a minimum washout period of 7-14 days between periods.

Each subject will be admitted to the unit in the evening prior to Day 1 and remain resident until all assessments completed on D12. All subjects will be scheduled for a follow up visit, 7-10 days after their final dose.

The overall maximum duration (screening to follow-up) for participating subjects will be about 13 weeks.

Protocol waivers or exemptions are not allowed. Therefore, adherence to the study design requirements, including those specified in the Time and Events Table, are essential

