#### **4.5.3. Other Dose Adjustment/Stopping Safety Criteria**

A subject will be withdrawn from the study if they meet the following stopping criteria:

- Subjects experience intolerable adverse events related to study drug.
- Subjects demonstrate clinically significant and relevant ECG changes.
- Subjects demonstrate clinically significant and relevant changes in laboratory parameters
- Subjects experience resting pulse increases of 40 bpm above the baseline resting heart rate or to a maximum of 130bpm at 2 successive measurements, a minimum of 5 minutes apart and if in the investigator's opinion, following a review of the subject's safety data and discussion with the GSK medical monitor, there are safety concerns.

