**Table 3 Detailed Time and Events Table for Day 1**

| Procedure                                |          | Day1  |       |        |        |        |    |      |    |    |    |    |     |
|------------------------------------------|----------|-------|-------|--------|--------|--------|----|------|----|----|----|----|-----|
|                                          | Pre-dose | 0 min | 5 min | 15 min | 30 min | 45 min | 1h | 1.5h | 2h | 4h | 6h | 8h | 12h |
| Dosing                                   |          | X     |       |        |        |        |    |      |    |    |    |    |     |
| Vital Signs (BP and HR)                  | X        |       | X     | X      |        | X      |    | X    |    | X  |    | X  |     |
| 12-lead ECG                              | X        |       |       | X      |        | X      |    | X    |    | X  |    | X  |     |
| Blood PK sampling                        | X        |       | X     | X      | X      |        | X  |      | X  | X  | X  | X  |     |
| SAE/AE/concurrent medication questioning | X        |       |       |        |        |        |    |      |    |    |    |    |     |

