**Electrocardiogram (ECG)**

- 12-lead ECGs will be obtained at each timepoint during the study using an ECG machine that calculates the heart rate and measures PR, QRS, QT, and QTcF intervals. Refer to Section 4.5.2 for QTcF withdrawal criteria and additional QTcF readings that may be necessary.
- Twelve-lead ECGs will be performed at screening, at various occasions throughout the treatment periods and at the follow-up visit as outlined in Section 4.6. Time and Events Table.
- Three measurements will be taken at screening and pre-dose, 1-5mins apart. The mean value recorded pre-dose will be classed as baseline.
- ECG measurements will be made (1-5mins apart for repeat measurements) with the subject in a supine having rested in this position for at least 5 mins before each reading.
- ECG-related stopping criteria for subjects are described in Section 4.5.2.

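### The vital-sign baseline is one screening mean for all three resident periods, up to about 10 weeks before Period 3, although Day 1 pre-dose readings exist in every period

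*Protocol*

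**What the plan says.** Protocol Section 7.2, Vital Signs, specifies "Three measurements will be taken at screening, 1 – 5mins apart" and continues "The mean value recorded will be classed as baseline". This gives one value per subject, taken seated, with no reference to period.

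The ECG part of the same section also asks for three measurements before dosing and states "The mean value recorded pre-dose will be classed as baseline". ECGs are taken supine, and the machine also reports heart rate.

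On timing, Section 4.1 says "All subjects will attend the unit for screening within 21 days of their first of three dosing periods", that "there will be a minimum washout period of 7-14 days between periods", and, for each period, "Each subject will be admitted to the unit in the evening prior to Day 1 and remain resident until all assessments completed on D12". It puts the maximum from screening to follow-up at about 13 weeks.

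Section 4.6 already has vital signs before the dose: "Table 3 Detailed Time and Events Table for Day 1" has a pre-dose reading, and Table 2 adds one on Day -1. Table 2 marks triplicate vital signs for screening only.

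Section 4.5.3 uses a baseline in one withdrawal criterion: "Subjects experience resting pulse increases of 40 bpm above the baseline resting heart rate". It does not say which baseline is meant. Section 6.3.2.4 plans descriptive safety summaries and leaves the detail to the Reporting and Analysis Plan (RAP).

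**The concern.** In a three-period crossover, a baseline measured before each period removes whatever has changed in the subject or the setting since entry. A single screening value does not. Screening is a unit visit. The later readings come from resident stays with standardised meals, fasting around dosing on Days 1 and 10, and no caffeine from 24 hours before dosing (Sections 8.2 and 8.3). The caffeine and fasting rules are tied to dosing, not to screening, so a difference in resting heart rate or blood pressure between the two settings is plausible, though its direction is not given.

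All five regimens contain active drug. If a summary shows mean change from the screening baseline by regimen, a visit shift common to all regimens looks the same as a drug effect common to all regimens. Section 1.3 names tachycardia as a monitored effect of both drug classes, so the absolute heart-rate change is a figure readers will look at.

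Separately, heart rate has two defined baselines, from different visits and in different postures, while the pulse criterion in 4.5.3 names neither.

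**Working it through.** **Inputs (Sections 4.1, 4.3 and 7.2).** Screening up to 21 days before first dose; 10 dosing days, residence to Day 12; washout 7 to 14 days; follow-up 7 to 10 days after the last dose; 20 sequences, three periods. The protocol does not say whether washout runs from the last dose (Day 10) or discharge (Day 12), nor whether it is a date difference or full days between, so four counts are shown.

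**Step 1: reproduce the stated maximum duration.** Period 3 Day 1 = 21 + 2 × step. Follow-up = that + 9 days to Day 10 + 10 days.

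| Washout counted | Step (days) | Screening to Period 3 Day 1 | Screening to follow-up |
|---|---|---|---|
| From Day 10, date difference | 9 + 14 = 23 | 67 | 86 |
| From Day 10, full days | 10 + 14 = 24 | 69 | 88 |
| From Day 12, date difference | 11 + 14 = 25 | 71 | 90 |
| From Day 12, full days | 12 + 14 = 26 | 73 | 92 |

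The last column is 12.3 to 13.1 weeks, which matches the stated figure of about 13 weeks.

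**Step 2: age of the baseline.** On the same calendar, the screening value is at most 67 to 73 days old (9.6 to 10.4 weeks) on Day 1 of Period 3 and 76 to 82 days old on Day 10. The washout is called a minimum, so its upper limit is unclear, but the overall maximum bounds the gap: reading 13 weeks as 91 days, 91 − 19 = 72 days to Period 3 Day 1. At the other extreme (screening one day before dosing, 7-day washouts, date difference), the gap is 1 + 2 × 16 = 33 to 1 + 2 × 18 = 37 days. A same-period pre-dose value is taken on the same day as the Day 1 post-dose readings.

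**Step 3: what a visit shift does.** Let S be a subject's screening value and Y(r) the reading on regimen r. If the resident level differs from S by d with no drug effect, then Y(r) − S = d on every regimen. Illustration with assumed shifts of −5, −6 and −7 bpm in Periods 1, 2 and 3: each regimen occurs four times in each period, so every regimen mean is

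[4(−5) + 4(−6) + 4(−7)] / 12 = −72/12 = −6.0 bpm,

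against 0.0 with the pre-dose baseline. Reversing the assumed signs gives +6.0.

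**Step 4: what it does not do.** Within a subject, [Y(A) − S] − [Y(C) − S] = Y(A) − Y(C). The screening value drops out. Each pair of regimens occurs together in 6 of the 20 sequences.

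**Step 5: price of a single reading.** Assume between-visit SD v and within-visit SD w. For Day 1 changes:

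- screening triplicate mean: variance = w²/3 + w² + 2v²
- single same-day pre-dose reading: variance = 2w²

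The single reading is the less variable choice when 2v² > (2/3)w², that is, when v > 0.58w. With v = w = 5 bpm the SDs are 9.13 and 7.07; with v = 3 and w = 5 they are 7.16 and 7.07. For Day 10 changes the single Day 1 reading is nine days old. If day-to-day variation within a stay were as large as between visits, its variance would be 2w² + 2v², an SD of 10.0 against 9.13 at v = w = 5. All these SDs are assumptions.

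**The case against.** The strongest reply is that the protocol plans no analysis that subtracts this baseline. The vital-sign endpoint in Section 3.2 is not expressed as a change, and Section 6.3.2.4 leaves the summaries to the RAP, which is not at hand and might define another baseline. That stands as a limit on the harm. It does not remove the point, because Section 7.2 states the rule outright: a RAP that follows it inherits the problem, and one that departs from it contradicts the protocol.

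A reader might infer more than the documents support:

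- **That the vilanterol effect on heart rate could be hidden.** Regimens C and D contain no vilanterol, so A versus C and B versus D show its effect, and the screening value cancels in those within-subject contrasts (Step 4).
- **That the PK/PD work is biased.** Section 6.3.2.3 plots maximum and weighted mean heart rate, with no baseline subtracted.
- **That the mean changes are understated by a known amount.** Neither the size nor the sign of a shift is in the documents.
- **That 4.5.3 contradicts 7.2.** It speaks of resting pulse, which fits the vital-sign part of 7.2 better than the ECG part, and seated and supine measurements may properly have different baselines. The criterion also has an absolute limb, requires two successive measurements, and requires investigator and medical-monitor review. What remains is that the reference is not named.

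The screening baseline also has a real merit: it is a mean of three readings taken before any study drug.

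**Conclusion.** The point holds in a limited form. Section 7.2 fixes a vital-sign baseline that can be about 10 weeks old by Period 3 (67 to 73 days at most, depending on how washout is counted), while the ECG baseline is pre-dose and a same-period vital-sign reading is already scheduled. Any screening-to-resident difference enters the absolute change of every regimen one for one, and no placebo regimen can separate it. For an assumed 3 to 8 bpm difference in heart rate, the distortion is 3 to 8 bpm in either direction; the calendar gap by itself implies no particular value.

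This matters only if changes from that baseline are summarised. Regimen contrasts within subject and the PK/PD plots stand. The unnamed reference in 4.5.3 is a separate matter of clarity that an analysis plan cannot settle, because the criterion is applied during the stay.

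**What to change.** In Section 7.2, state that for descriptive change-from-baseline summaries of heart rate and blood pressure the baseline is the Day 1 pre-dose value of the same period, and carry this into the RAP. Confine the wording to summaries, so that it does not alter the reference for the withdrawal criterion by default.

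Separately, reconcile Section 4.5.3 with the two baseline definitions in Section 7.2, so that the pulse criterion names the measurement and visit it refers to. Which reference to use is for the sponsor and investigator to settle; none is proposed here.

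The cost is wording, since the readings are already scheduled. The drawback is a single reading in place of a triplicate mean. On the assumptions in Step 5 this need not cost precision on Day 1 but may cost some on Day 10. Taking the pre-dose vital signs in triplicate would remove that drawback, at the price of added measurements on Day 1 of each period.

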**Electrocardiogram (ECG)**

- 12-lead ECGs will be obtained at each timepoint during the study using an ECG machine that calculates the heart rate and measures PR, QRS, QT, and QTcF intervals. Refer to Section 4.5.2 for QTcF withdrawal criteria and additional QTcF readings that may be necessary.
- Twelve-lead ECGs will be performed at screening, at various occasions throughout the treatment periods and at the follow-up visit as outlined in Section 4.6. Time and Events Table.
- Three measurements will be taken at screening and pre-dose, 1-5mins apart. The mean value recorded pre-dose will be classed as baseline.
- ECG measurements will be made (1-5mins apart for repeat measurements) with the subject in a supine having rested in this position for at least 5 mins before each reading.
- ECG-related stopping criteria for subjects are described in Section 4.5.2.

## Clinical Laboratory Assessments

Hematology, clinical chemistry, urinalysis and additional parameters to be tested are listed below:

### Hematology

|                      |                     |                                    |
|----------------------|---------------------|------------------------------------|
| Platelet Count       | RBC Indices: | Automated WBC Differential: |
| RBC Count            | MCV                 | Neutrophils                        |
| WBC Count (absolute) | MCH                 | Lymphocytes                        |
| Hemoglobin           | MCHC                | Monocytes                          |
| Hematocrit           |                     | Eosinophils                        |
|                      |                     | Basophils                          |

### Clinical Chemistry

|                  |           |                      |                            |
|------------------|-----------|----------------------|----------------------------|
| BUN              | Potassium | AST (GOT)            | Total and direct bilirubin |
| Creatinine       | Calcium   | ALT (GPT)            | Uric Acid                  |
| Glucose, fasting |           | GGT                  | Albumin                    |
| Sodium           |           | Alkaline phosphatase | Total Protein              |

### Routine Urinalysis

|                                                           |
|-----------------------------------------------------------|
| Specific gravity                                          |
| pH, glucose, protein, blood and ketones by dipstick       |
| Microscopic examination (if blood or protein is abnormal) |

### Other screening tests

|                                                                            |
|----------------------------------------------------------------------------|
| HIV                                                                        |
| Hepatitis B (HBsAg)                                                        |
| Hepatitis C (Hep C antibody )                                              |
| FSH and estradiol (as needed in women of non-child bearing potential only) |
| Alcohol and urine cotinine screen                                          |

Further details regarding these tests can be obtained from the SPM.

## 7.3. Pregnancy

### 7.3.1. Time period for collecting pregnancy information

All pregnancies in female subjects and/or female partners of male subjects will be collected after the start of dosing and until follow-up visit.

### 7.3.2. Action to be taken if pregnancy occurs

The investigator will collect pregnancy information on any female subject, who becomes pregnant while participating in this study. The investigator will record pregnancy information on the appropriate form and submit it to GSK within 2 weeks of learning of a

subject's pregnancy. The subject will also be followed to determine the outcome of the pregnancy. Information on the status of the mother and child will be forwarded to GSK. Generally, follow-up will be no longer than 6 to 8 weeks following the estimated delivery date. Any premature termination of the pregnancy will be reported.

While pregnancy itself is not considered to be an AE or SAE, any pregnancy complication or elective termination of a pregnancy for medical reasons will be recorded as an AE or SAE.

A spontaneous abortion is always considered to be an SAE and will be reported as such. Furthermore, any SAE occurring as a result of a post-study pregnancy and is considered reasonably related to the study treatment by the investigator, will be reported to GSK as described in Section 12. While the investigator is not obligated to actively seek this information in former study participants, he or she may learn of an SAE through spontaneous reporting.

Any female subject who becomes pregnant while participating will be withdrawn from the study

